# Dihydroartemisinin-piperaquine or sulphadoxine-pyrimethamine for the chemoprevention of malaria in children with sickle cell anaemia in eastern and southern Africa (CHEMCHA): a protocol for a multi-centre, two-arm, double-blind, randomised, placebo-controlled superiority trial

**DOI:** 10.1186/s13063-023-07274-4

**Published:** 2023-04-05

**Keywords:** Malaria, Sickle cell anaemia, Chemoprevention, Mortality, Dihydroartemisinin-piperaquine, Sulphadoxine-pyrimethamine

## Abstract

**Background:**

An estimated 300,000 babies are born with sickle cell anaemia (SCA) annually. Affected children have chronic ill health and suffer premature death. Febrile illnesses such as malaria commonly precipitate acute crises in children with SCA. Thus, chemoprophylaxis for malaria is an important preventive strategy, but current regimes are either sub-optimally effective (e.g. monthly sulphadoxine-pyrimethamine, SP) or difficult to adhere to (e.g. daily proguanil). We propose dihydroartemisinin-piperaquine (DP) as the agent with the most potential to be used across Africa.

**Methods:**

This will be a randomised, double-blind, parallel-group superiority trial of weekly single-day courses of DP compared to monthly single-day courses of SP in children with SCA. The study will be conducted in eastern (Uganda) and southern (Malawi) Africa using randomisation stratified by body weight and study centre. Participants will be randomised using an allocation of 1:1 to DP or SP. We will investigate the efficacy, safety, acceptability and uptake and cost-effectiveness of malaria chemoprevention with weekly courses of DP vs monthly SP in 548 to 824 children with SCA followed up for 12–18 months. We will also assess toxicity from cumulative DP dosing and the development of resistance. Participant recruitment commenced on 30 April 2021; follow-up is ongoing.

**Discussion:**

At the end of this study, findings will be used to inform regional health policy. This manuscript is prepared from protocol version 2.1 dated 1 January 2022.

**Trial registration:**

The trial was registered at ClinicalTrials.gov, NCT04844099. Registered on 08 April 2021.

## Administrative information

Note: the numbers in curly brackets in this protocol refer to the SPIRIT checklist item numbers. The order of the items has been modified to group similar items (see http://www.equator-network.org/reporting-guidelines/spirit-2013-statement-defining-standard-protocol-items-for-clinical-trials/).

## Introduction

### Background and rationale {6a}

Sickle cell anaemia (SCA) is one of the most common inherited disorders in the world [1]. Patients suffer chronic morbidity and early mortality mainly due to severe complications related to hypoxia. It is estimated that SCA causes 5–16% of all under-5 mortality in sub-Saharan Africa. Although significant gains have been made, malaria too remains a major cause of morbidity and mortality in African children [2]. Children with the heterozygous sickle cell trait (HbAS) are strongly protected against severe malaria [3], and this is thought to be the main reason why the HbS gene has been retained in African populations. Children with the homozygous SCA also appear to have a lower risk of malaria compared to those without but may suffer much higher mortality if hospitalised with malaria [4]. The reasons for the increased risk may partly be related to worsened anaemia, sickle cell crises and bacteraemia that can occur with malaria. Thus, in many African countries, malaria chemoprevention is prescribed for the patients. However, due to high levels of parasite resistance, regimes such as monthly sulphadoxine-pyrimethamine (SP) that were recommended decades ago may now be sub-optimally effective. Despite this, guidelines in Uganda and Malawi, among others, still recommend monthly SP [5]. Daily regimes, e.g. daily proguanil, are recommended in other countries such as Kenya but are difficult to adhere to. In West Africa, the recommendations are even more unclear. For example, in Nigeria, SCA guidelines recommend daily proguanil, but the National Malaria Control Program recommends against this as proguanil may be ineffective. Instead, a policy of no chemoprevention but a test and treat strategy is recommended. Moreover, compared to eastern and southern Africa, a high burden of infections in West Africa is due to vivax malaria. The striking differences in aetiology and approach, coupled with the compelling but limited evidence that malaria is a major cause of mortality in SCA, provide a strong reason for multi-country studies.

Artemisinin-containing combination therapies (ACTs) such as DP are now the standard for the treatment of *Plasmodium falciparum* malaria in both children and adults [6]. A systematic review of the efficacy and safety of ACTs showed that DP is very effective and provides a long duration of post-treatment prophylaxis similar to mefloquine and a longer duration than amodiaquine or lumefantrine-based combinations [6, 7]. Because of its long half-life, piperaquine has great potential for use as the ACT of choice for intermittent treatment and chemoprophylaxis, as was shown in intermittent preventive treatment (IPT) studies in children [8]. We propose dihydroartemisinin-piperaquine as the chemopreventive agent of choice for children with SCA on the continent.

A trial with monthly DP used as IPT in Thai adults showed it to be well-tolerated, safe and highly effective [9]. The most important determinant of protective efficacy was the trough plasma concentration of piperaquine, and this was determined by the dosing frequency. The study suggested that for effective prevention of malaria, DP should at least be given monthly to achieve steady-state concentrations above the minimum inhibitory concentrations and sustained prophylactic levels. Piperaquine is currently only available in the fixed-dose combination with dihydroartemisinin (DHA) as DP. The DHA component, eliminated within a few hours, is not expected to contribute significantly to chemoprevention effects, yet may provide a degree of protection against the development of piperaquine resistance in the population.

Side effects of DP in adults include transient drops in haemoglobin by day 7 (seen with all ACT), headache, weakness, and fever. Its main safety concerns relate to its dose-dependent QT prolongation seen in clinical trials, including our post-discharge chemoprevention of malaria in transfused children (PMC) study [10]. Nevertheless, the side effects of DP are mild and similar to that seen with other anti-malarial drugs [11]. There is also no indication from the data signalling that it is associated with clinically significant arrhythmia [12].

On the other hand, SP is one of the most successful drugs for malaria prophylaxis [13]. In Uganda, monthly SP was more efficacious than weekly chloroquine in malaria prophylaxis in children with SCA [14]. However, this combination has increasingly become ineffective in Africa [15]. Resistance is mediated through mutations at the genes encoding *P. falciparum* dihydrofolate reductase (Pfdhfr) and dihydropteroate synthase (Pfdhps). In eastern and southern Africa, more than 90% of parasites harbour up to three mutations in the dihydrofolate reductase [dhfr] gene and two mutations in the dihydropteroate synthase [dhps] gene [16, 17]. This high-level burden of resistance genes may mean ineffective malaria chemoprevention. In this trial, we aim to determine the efficacy and safety of malaria chemoprevention with weekly single-day courses of DP compared to monthly single courses of SP (the standard of care).

## Objectives {7}

### Primary objective

The study objective is to determine the efficacy and safety of malaria chemoprevention with weekly single-day courses of DP compared to monthly single courses of SP in children with SCA in eastern and southern Africa.

### Secondary objectives

Assess the feasibility and stakeholder perceptions on the uptake (acceptability) and the potential for future roll-out of weekly DP vs monthly SPDetermine the safety of cumulative dosing of DP, especially on cardiac functionMonitor the development of malaria parasite resistance to DP in clinical isolates over timeAssess patients’ health-related quality of life, cost-effectiveness, equity and economic implications of using weekly courses of DP vs monthly courses of SP as chemoprevention in SCAConduct policy advocacy to engage key stakeholders on policy decisions on using weekly courses of DP or monthly courses of SP for the chemoprevention of malaria in SCA

## Trial design {8}

This is a multi-centre, parallel-group, two-arm, double-blind, individually randomised superiority trial with a 1:1 allocation ratio comparing the efficacy, safety, acceptability, uptake and cost-effectiveness of malaria chemoprevention with weekly courses of DP or monthly SP in children with SCA in eastern (Uganda) and southern (Malawi) Africa. Randomisation to either weekly DP + monthly SP-*placebo* or monthly SP + weekly DP-*placebo* is by varying block sizes and stratified by study site and weight. The primary outcome is the incidence of clinical malaria defined as a history of fever in the preceding 48 h or documented axillary temperature ≥ 37.5 °C plus *Plasmodium falciparum* parasites on microscopic examination of a blood smear.

## Methods: participants, interventions and outcomes

### Study setting {9}

This study is being conducted in Uganda and Malawi. These two countries have moderate to intense malaria transmission. The study sites in Uganda are Jinja Regional Referral Hospital (Jinja) and Kitgum General Hospital (Kitgum), while in Malawi, the sites are Queen Elizabeth Central Hospital (Blantyre) and Kamuzu Central Hospital (Lilongwe). The two countries have similar guidelines and high parasite resistance rates to SP [18]. Jinja Regional Referral Hospital in east-central Uganda is a 250 referral centre on the shores of Lake Victoria. Kitgum General Hospital is a 100-bed district hospital in northern Uganda. Both hospitals serve areas with very high malaria transmission. The SCA clinic in Jinja runs weekly attending to about 80 outpatients. The one in Kitgum hospital is less developed and will be built further by study onset. In Malawi, the 1000-bed Queen Elizabeth Central Hospital is the largest tertiary hospital in the country. It has a long-standing paediatric SCA clinic serving over 400 children in southern Malawi. The dedicated SCA clinic in Kamuzu Central hospital was created in 2015 and, by the time of study onset, had over 200 patients on hydroxyurea treatment. In all four clinics, patients attend outpatient follow-up care every 1–3 months, and the guidelines for care are similar.

### Eligibility criteria {10}

#### Inclusion criteria

The inclusion criteria for enrolment are:Children with a diagnosis of SCA *(HbSS)* on haemoglobin electrophoresis, high-performance liquid chromatography (HPLC) or isoelectric focusingAged between 6 months and 15 yearsWeight of 5 kg or higherWritten informed consent from a parent or legal guardian and assent by the child (if aged 8 years or older)

The upper age limit of 15 years was chosen based on both a pragmatic approach of being able to recruit most patients attending SCA clinics and the lower incidence of malaria in adolescents beyond this age. Around Jinja, the incidence of malaria in children with normal haemoglobin (HbAA) declines by over 50% in adolescents 15–18 years compared to those 11–15 years ([name], unpublished).

#### Exclusion criteria

Participants presenting with an acute illness on enrolment will first receive treatment for the acute event and be recruited when symptoms resolve.

The exclusion criteria were:Those with an additional chronic disease such as known congenital heart diseaseThose with a known allergy to DP or SPOther known red cell disorders, e.g. thalassaemia, G6PD deficiencyThose receiving daily cotrimoxazole prophylaxisThose unlikely to comply with the follow-up scheduleThose participating in another trial

### Who will take informed consent? {26a}

Parents/guardians of children who fulfil the screening eligibility criteria will be approached and invited to the study clinic to provide written consent. Children 8 years or older will also be asked for assent. The consent (and assent where appropriate) will be obtained by the study nurse. The consent document will be provided in English or a local language understood by the parent/carer and participant.

### Additional consent provisions for collection and use of participant data and biological specimens {26b}

Separate consent will be sought for genetic testing, ECG and pharmacokinetic testing, for long-term storage and shipping of samples to external labs and for future research that may have no immediate clinical relevance.

### Interventions

#### Explanation for the choice of comparators {6b}

##### The rationale for the choice of DP for chemoprevention

SP is currently the anti-malarial drug of choice for malaria chemoprevention in SCA in most of sub-Saharan Africa. However, there is high-grade resistance to SP in many parts of the continent and Asia. Because of the long half-life of piperaquine (median 14 [range 10–18] days in children) [19, 20], DP provides 1 to 2 weeks longer post-treatment prophylaxis than other ACTs such as artemether-lumefantrine or amodiaquine-artesunate [21]. Amodiaquine has been evaluated (alone or combined with SP) for IPTp in Ghana. However, one of the amodiaquine arms was stopped prematurely because the drug was not well tolerated. Mefloquine provides a similar longer duration of prophylaxis compared to piperaquine, but mefloquine too is not well tolerated.

##### The rationale for once-weekly prophylaxis instead of monthly DP

Three pharmacological modelling groups have shown that in pregnant women, adults, and children, compared with monthly dosing, once-weekly DP would potentially lead to substantially higher steady-state piperaquine trough concentrations and result in a higher proportion of individuals attaining trough concentrations above the minimum inhibitory concentrations, while at the same time lowering the peak concentrations and the associated risk of QT prolongation [22–25]. Weekly DP is therefore predicted to be more effective than monthly dosing at preventing new infections and also exerting less selection pressure for piperaquine resistance. Importantly, these models also suggested that weekly dosing is more favourable than monthly administration in terms of missing occasional doses [23]. Moreover, although all three groups showed that the use of a loading dose with the standard 3-day regimen will reduce the time to reach steady-state concentrations, even without a loading dose, this can still be reached within 1 month [22–25]. Daily prophylaxis with low doses of DP was predicted to be even more favourable in terms of skipping doses than weekly or monthly regimens but was not considered an option for our trial because of the expected high pill burden in addition to others such as daily penicillin V, folic acid, and hydroxyurea. Daily or weekly prophylaxis with piperaquine monotherapy (i.e. without the DHA component) was not considered for this trial as (1) it is not currently available and (2) it would mean introducing monotherapy with piperaquine onto the market with the associated risk of development of parasite resistance.

#### Intervention description {11a}

Participants will be randomly allocated to receive one of two medications: weekly DP + monthly SP placebo or monthly SP + weekly DP placebo.

##### Dihydroartemisinin piperaquine (DP)

The study will use the scored dispersible tablets of D-ARTEPP® from Guilin Pharmaceutical Co. Ltd. D-ARTEPP is a WHO pre-qualified ACT. It is registered in both Uganda and Malawi. It will be provided as the co-formulated DHA (20 mg) and piperaquine (160 mg) and administered once weekly at approximate doses of DHA 2.5 mg/kg/day and piperaquine 20 mg/kg/day based on participants’ weight categories.

##### Sulphadoxine-pyrimethamine (SP)

The active control will be SP, the current standard of care for malaria chemoprevention for SCA in Uganda and Malawi. This will also be provided by Guilin Pharmaceutical Co. Ltd as their generic WHO-approved 500/25 mg tablets. It will be administered as monthly single-day courses of SP at approximate doses of S = 25 mg/kg and P = 1.25 mg/kg.

##### Placebo

Participants receiving weekly DP will in addition receive a single monthly dose of tablets identical to SP (SP-placebo). Those randomised to receive monthly SP will in addition receive weekly doses of tablets identical to DP (DP-placebo). In both trial arms, the dose and administration procedures will be identical to that for the active drugs.

#### Criteria for discontinuing or modifying allocated interventions {11b}

Participants will be withdrawn from study interventions for suspected or confirmed allergic reactions to the study drugs or for safety reasons as judged by the investigator, study safety monitor or the data safety and monitoring board (DSMB). Participants diagnosed with symptomatic uncomplicated malaria anytime during the study (unscheduled visits) will be treated with artemether-lumefantrine and where appropriate the next weekly dose of DP or the monthly dose of SP delayed.

#### Strategies to improve adherence to interventions {11c}

Right from the outset, participants and their parents/carers will be counselled on adherence to study medications. Adherence monitoring will be checked by a count of the remaining medication at every study visit. At all study visits, in addition to safety monitoring, residual pill counts will be performed to assess adherence and any challenges to that schedule. Subjects with more than a few residual tablets will be identified as less adherent to study requirements. Counselling will focus on the importance of adherence, and we will work with parents to troubleshoot issues. Parents will also be reminded not to share the study drug with siblings or other family members.

#### Relevant concomitant care permitted or prohibited during the trial {11d}

##### Routine care, outpatient care and permitted concomitant medication

Study participants will receive the current standard of care. All care directly related to the proper and safe conduct of the trial, and the treatment of immediate adverse events related to trial procedures will be provided free of charge by the study in the study hospitals. The provision of ancillary care beyond that immediately required for the conduct of the trial will not be covered by the trial. Thus, in addition to the study drugs:Parents/carers will be educated on the care of children with SCA. This will include sessions on daily activities including play and hydration, care of the child on hot and cold days, pain management, and when to seek medical helpAll will be supplied with a course of paracetamol for pain eventsParticipants will also receive standard-of-care therapy and prophylaxis including:◦ Daily folic acid◦ Oral penicillin for children < 5 years◦ The immunisation of the child will be updated◦ Participants will be requested to attend the study clinic every 2 months

Because of concerns about drug-drug interactions between SP and folic acid and the potential impact on malaria chemoprophylaxis [26], folic acid supplementation will be provided at the internationally recommended dose of 0.4 mg daily.

##### Hospitalisation and inpatient care

The following will necessitate hospitalisation and inpatient care:Development of severe complications including severe anaemia (Hb < 5 g/dl), severe pain episodes/vaso-occlusive crises, stroke, acute chest syndrome, mesenteric crisis, hyper haemolytic crisis and a hepatic crisis among othersIn addition to a blood slide for malaria parasites, participants presenting with axillary temperature > 38.0 °C will have blood and urine cultures taken and be given iv antibiotics (ceftriaxone). Further management will depend on blood slide, fever response and culture results. An episode of malaria will be defined as fever plus the presence of *P. falciparum* on a blood smear. Severe malarial anaemia will be defined as the presence of *P. falciparum* on blood smear and haemoglobin ≤ 5 g/dL. During the treatment and follow-up phase of the study, if a subject is diagnosed with malaria, the investigator will prescribe antimalarial treatment based on the severity of the malaria illness. The World Health Organization criteria will be used to classify children as having severe or uncomplicated malariaNeed for surgical procedures

Hospitalised participants will be managed according to local standard guidelines. The standard in-hospital care for severe anaemia includes a blood transfusion (20 ml/kg whole blood or 10 ml/kg packed red cells). If this is due to malaria, the child will in addition receive parenteral artesunate (2.4 mg/kg at times 0, 12, and 24 h [children weighing < 20 kg will receive a higher dose of artesunate—3 mg/kg per dose]) and thereafter once the patient can take orally, a full 3-day course of artemether-lumefantrine.

##### Prohibited medication

Prohibited medication includes antimalarial drugs not prescribed within the trial protocol and other drugs with antimalarial properties such as co-trimoxazole. Therefore, concomitant use of the antimalarials mefloquine, halofantrine, tetracyclines, artemisinin derivatives, sulphadoxine/pyrimethamine, atovaquone-proguanil (Malarone) and chlorproguanil-dapsone (Lapdap™) are not allowed from baseline until end of the study. Randomised participants who take prohibited medications will remain in the trial and will be included in the primary, intention-to-treat analysis, but excluded from the per-protocol analysis.

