### Outcomes {12}

#### Primary efficacy outcome

The primary efficacy outcome is the incidence of clinical malaria defined as a history of fever in the preceding 48 h or documented axillary temperature of ≥ 37.5 °C, plus *P. falciparum* parasites on microscopic examination of a blood smear by a certified malaria microscopist.

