#### Sensitivity analyses

Several sensitivity analyses will be conducted to assess the robustness of the primary endpoint analysis. These include an analysis of the PP subject population and a covariate-adjusted analysis. Other regression models will also be explored. Additional post hoc analyses may also be conducted if deemed appropriate. In addition, we will compare the results of the covariate-adjusted analyses with and without imputation for missing values for covariate values at baseline.

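### The per-protocol rule deletes outright any child given an antimalarial outside the study, even when it was given for malaria, so the supportive analysis selects on a consequence of the outcome

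*Protocol article*

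**What the plan says.** *Prohibited medication* opens with a definition: "Prohibited medication includes antimalarial drugs not prescribed within the trial protocol and other drugs with antimalarial properties such as co-trimoxazole". A list introduced as following from it says that "mefloquine, halofantrine, tetracyclines, artemisinin derivatives, sulphadoxine/pyrimethamine, atovaquone-proguanil (Malarone) and chlorproguanil-dapsone (Lapdap™) are not allowed from baseline until end of the study". The consequence for analysis comes next: "Randomised participants who take prohibited medications will remain in the trial and will be included in the primary, intention-to-treat analysis, but excluded from the per-protocol" set.

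The protocol itself prescribes drugs of the listed classes. *Criteria for discontinuing or modifying allocated interventions {11b}* says that children with symptomatic uncomplicated malaria "will be treated with artemether-lumefantrine and where appropriate the next weekly dose of DP or the monthly dose of SP delayed". For severe anaemia, *Hospitalisation and inpatient care* says: "If this is due to malaria, the child will in addition receive parenteral artesunate". The study drugs are SP and a combination containing dihydroartemisinin.

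*Analysis populations* makes intention-to-treat primary and per-protocol supportive. It defines the per-protocol population as a subset of subjects, so an excluded child goes with all of its follow-up. It calls this set important for cost-effectiveness and leaves major deviations to the SAP. *Sensitivity analyses* names it as a robustness check on the primary endpoint: "These include an analysis of the PP subject population and a covariate-adjusted analysis".

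**The concern.** The primary outcome is clinical malaria, and malaria is what leads to antimalarial treatment. Episodes treated under the protocol are covered by the exemption. Episodes treated elsewhere are not, and the article foresees events away from the study: scheduled visits are two months apart, and *Plans for assessment and collection of outcomes {18a}* provides for recording events for which the child did not attend the study clinic. A child given an antimalarial at another facility has taken one not prescribed within the protocol and leaves the per-protocol set completely, including event-free time before that illness.

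Membership of the set then depends on something that happens after randomisation and that the intervention is meant to reduce. If DP works, more SP children are removed, and they tend to be those at higher risk. What remains of the SP arm looks healthier than it should, which pulls the rate ratio towards 1. At stake is the value of a named robustness check and of the set linked to cost-effectiveness.

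Separately, the list does not restate the exemption, so whoever codes the per-protocol set has two sentences that do not match.

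**Working it through.** **Inputs from the article.** SP rate 0.2 and DP rate 0.1 per person-year, 18 months (T = 1.5 years), power 0.9, significance level 0.05 (taken as two-sided), 20% loss, 274 per group (*Sample size {14}*).

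**Assumed, not in the documents.** Share *f* of episodes treated outside the study, equal in both arms: 10%, 25%, 50%. Variance *k* of a gamma-distributed, mean-1 risk multiplier between children: 0, 1, 2.

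**1. The plan's own figure.** Person-years per arm = (1.960 + 1.282)² × (1/0.2 + 1/0.1) / (ln 0.5)² = 328.05. Dividing by 1.5 gives 219 per arm, 438 in total; 438/0.8 = 548. Both figures reproduce, so these rates are the planning basis.

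**2. Children removed.** With Poisson counts, no between-child variation and full follow-up, the share with at least one outside-treated episode is 1 − exp(−r·f·T).

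| f | SP (r = 0.2) | DP (r = 0.1) |
|---|---|---|
| 10% | 1 − exp(−0.030) = 3.0% | 1 − exp(−0.015) = 1.5% |
| 25% | 1 − exp(−0.075) = 7.2% | 1 − exp(−0.0375) = 3.7% |
| 50% | 1 − exp(−0.150) = 13.9% | 1 − exp(−0.075) = 7.2% |

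At f = 25% that is about 20 and 10 of 274 children.

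**3. Effect on the rate ratio.** A child with risk multiplier *u* stays in the set with probability exp(−u·r·f·T). Among children who stay, the mean multiplier is 1/(1 + k·r·f·T), so the remaining rate is r(1 − f)/(1 + k·r·f·T). With rT = 0.3 for SP and 0.15 for DP, (1 − f) cancels:

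ratio = 0.5 × (1 + 0.3kf)/(1 + 0.15kf)

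| k | f = 10% | f = 25% | f = 50% |
|---|---|---|---|
| 0 | 0.500 | 0.500 | 0.500 |
| 1 | 0.5 × 1.03/1.015 = 0.507 | 0.5 × 1.075/1.0375 = 0.518 | 0.5 × 1.15/1.075 = 0.535 |
| 2 | 0.5 × 1.06/1.03 = 0.515 | 0.5 × 1.15/1.075 = 0.535 | 0.5 × 1.3/1.15 = 0.565 |

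The shift is towards 1 whenever children differ in risk, and absent when they do not.

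**The case against.** **A stronger reading that fails.** A reader might infer that every child with a treated primary event is excluded, because the list bars artemisinin derivatives and the protocol treats malaria with them. At the planned rates that would be 1 − exp(−0.3) = 25.9% of SP and 1 − exp(−0.15) = 13.9% of DP children, or 71 + 38 = 109 of 548. If every episode were so treated, no events would be left to analyse. The document does not support this. The definition is limited to antimalarials not prescribed within the protocol, and the list is drawn from that definition. Taken literally, the list would also bar SP and the dihydroartemisinin in DP, excluding every dosed child in both arms. It cannot be meant that way. Only the need to reconcile the wording stands.

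**Outside treatment is not the primary outcome.** A primary event needs a smear read by a certified microscopist, so an episode treated elsewhere may never be counted, even under intention-to-treat. This stands: one cannot say that the rule loses a given share of primary events. The rate-ratio calculation survives because (1 − f) cancels. Presumptive treatment of fevers that are not malaria would also remove children, without necessarily favouring either arm.

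**The share may be small.** The study offers sick-visit care and refunds clinic transport. At f = 10% the ratio moves only to 0.507–0.515. This also stands, and it rules out saying that the per-protocol analysis cannot test robustness at all.

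**The SAP may settle it.** It may define other major deviations, but this exclusion is stated in the protocol and not deferred. An SAP that handled it differently would depart from the protocol's text.

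**The rule is conventional.** Excluding users of non-protocol antimalarials is common, and censoring at first use also conditions on events after randomisation. Both are true. Censoring nevertheless keeps the child's earlier follow-up.

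**Conclusion.** The point holds in a limited form. The protocol fixes a whole-child, post-randomisation exclusion that can be triggered by malaria or febrile illness treated outside the study, and it is expected more often under SP. The likely effect is modest attenuation of the per-protocol rate ratio: 0.50 to 0.52–0.57 for an outside-treated share of 25–50% and a gamma variance of 1–2, less for a smaller share, and none without between-child variation. The share, its equality between arms and the variance are all assumptions; the document gives none of them. Only the supportive and sensitivity analysis is affected. The primary intention-to-treat analysis keeps these children. This is worth correcting because the correction is cheap, but it does not threaten the trial's main conclusion.

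**What to change.** Add to *Prohibited medication*, and mirror in the SAP:

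- For defining the per-protocol population only, antimalarials given to treat a malaria episode, by the study or elsewhere, do not trigger exclusion. Say whether presumptive treatment of a fever counts as treating an episode.
- For other prohibited use, such as non-study chemoprevention or co-trimoxazole, censor the child's per-protocol follow-up at the date of first use instead of deleting the child from baseline.
- Reconcile the drug list with the definition that precedes it, with the two study-drug descriptions, and with the malaria treatment in *Criteria for discontinuing or modifying allocated interventions {11b}* and *Hospitalisation and inpatient care*.

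The cost is a sentence or two. *Concomitant therapy* already provides for recording indications and dates, so no new data are needed. The downside is that some unsupervised antimalarial exposure stays in the per-protocol set. No change to treatment is implied.
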